# Vascular Impulse Technology versus elevation in the treatment of posttraumatic swelling of extremity fractures: study protocol for a randomized controlled trial

**DOI:** 10.1186/s13063-017-1824-8

**Published:** 2017-02-16

**Keywords:** Posttraumatic swelling, Elevation, Vascular impulse, Cryotherapy, Upper extremity, Lower extremity, Intermittent pneumatic compression

## Abstract

**Background:**

Fractures of the extremities are often complicated by a variable degree of swelling secondary to hemorrhage and soft tissue injury. Patients typically require up to 7 days of inpatient bed rest and elevation to reduce swelling to an acceptable level for operative treatment with internal fixation. Alternatively, an intermittent pneumatic compression device, such as the Vascular Impulse Technology (VIT) system, can be used at the injured extremity to reduce the posttraumatic swelling. The VIT system consists of a pneumatic compressor that intermittently rapidly inflates a bladder positioned under the arch of the hand or the foot, which results in compression of the venous hand or foot plexus. That intermittent compression induces an increased venous velocity and aims to reduce the soft tissue swelling of the affected extremity.

**Methods/design:**

The VIT study is a prospective, monocenter, randomized controlled trial to compare the VIT system with elevation in the treatment of posttraumatic swelling in the case of a fracture of the upper and lower extremity. This study will include 280 patients with fractures of the upper and the lower extremity with nine different injury types. For each of the nine injury types a separate randomization to the two intervention groups (VIT group or control group) will be performed. The primary outcome parameter is the time taken for the swelling to resolve sufficiently to permit surgery. A separate analysis for each of the nine injury types will be performed.

**Discussion:**

In the proposed study, the effectiveness of the VIT system in the treatment of posttraumatic swelling of upper and lower extremity fractures will be evaluated.

**Trial registration:**

German Clinical Trial Register, No. DRKS00010510. Registered on 17 July 2016.

**Electronic supplementary material:**

The online version of this article (doi:10.1186/s13063-017-1824-8) contains supplementary material, which is available to authorized users.

## Background

### Background and rationale

Fractures of the upper and the lower extremity with involvement of the joint are, in general, associated with damage to the articular surface. Operative treatment with open reduction and internal fixation is, therefore, recommended for most of these fractures [1–6]. However, the treatment is often complicated by a variable degree of swelling secondary to hemorrhage and soft tissue injury [7–9]. Many of these fractures develop severe swelling that precludes operative intervention until adequate edema resolution has commenced [8, 9]. Patients typically require up to 7 days of inpatient bed rest and elevation of the injured extremity to reduce swelling to an acceptable level for operative treatment with internal fixation [9]. Postoperative swelling of the soft tissue is often responsible for complications, such as compartment syndrome, or local wound problems such as skin necrosis or wound infection [10]. Beside this, the perioperative swelling of the soft tissue is often accompanied by pain leading to prolonged immobilization and the need for strong painkillers with their associated complications. Delay in surgery impacts the patient in the short term but also increases the burden on an orthopedic inpatient trauma unit by prolonging the preoperative interval and total hospital stay [11].

Numerous interventions have been developed to control soft tissue swelling including elevation, compressive dressings and splint immobilization [12–15]. More recently, cryotherapy and intermittent pneumatic compression (IPC) devices have been employed. The IPC devices were first described in the medical literature in 1992 [16]. The main application area of these devices is as antithrombotic therapy, and many reports have been published to prove their antithrombotic effect [16–19]. Beside this, some IPC devices have different pump characteristics but generally tend to rapidly inflate to a pressure of approximately 100 mmHg in less than half a second (Fig. 1). These systems have been shown to stimulate venous return in the immobile lower limb as effectively as walking [20].

**Fig. 1 Fig1:**
[figure not shown]
Schematic illustration of the application and the mechanism of the VADOPlex foot-pump system (with kind permission of the Fa. OPED, http://oped-international.com/)

Several studies have shown each of these to be effective in reducing edema faster than simple elevation and immobilization [20, 21]. The use of an impulse foot-pump system has previously been shown to reduce edema by means of measurement of ankle and toe girths [10, 11, 20]. The clinical advantages of these devices have been determined in the treatment of ankle fractures and calcaneal fractures [10, 11, 13, 14, 20]. The hospitalization period and surgical site infections were reduced in the patients who received the impulse foot-pump system compared to the control group with elevation. However, the effectiveness of the impulse foot-pump system has not yet been investigated in detail, as complications such as postoperative skin necrosis and compartment syndrome, and the amount of pain medication required have not been determined. Furthermore, data for the impulse foot-pump system are only available for its use in the treatment of ankle and calcaneal fractures.

### Preliminary data

One randomized controlled trial that included 54 patients with ankle fractures compared an impulse foot-pump system with elevation and plaster in the treatment of preoperative swelling [20]. The results of this trial showed a significant reduction in time taken for ankle swelling to settle prior to surgery in the patients using the impulse system, together with a reduction in wound and skin complications (11% versus 44%; *p* < 0.01) and final preoperative ankle swelling (13 mm ± 13 versus 24 mm ± 17; *p* = 0.03). This study was the first to address the issue of whether the impulse foot-pump system has preoperative clinical value in an unselected group of patients with ankle fractures. This study is limited by the fact, that only patients with ankle fractures have been included and that the impulse system was only used in preoperative management. The authors, therefore, concluded that a further randomized controlled trial would be useful to prove the additional benefit in continuing foot-pump therapy in the postoperative phase.

Another study analyzing the effectiveness of the impulse system was published in 2013 [11]; Dodds et al. reported about 64 patients with closed ankle fractures using the impulse system prior to surgery. These patients were compared with a retrospective control group of 73 consecutive patients with closed ankle fractures managed surgically in the same unit immediately prior to the implementation of the impulse device study. The results of this study have shown that the median length of time to surgery, hospital stay duration and surgical site infections were significantly reduced in the study group as compared to the control group. This study is limited by the retrospective nature of the control group. Furthermore, more than half of the patients in the control group and in the study group had an isolated fracture of the medial or lateral malleolus. These fractures are benign regarding soft tissue swelling and do not require special treatment for swelling in general.

There are five more studies available in the medical literature that examined the clinical advantage of impulse foot-pump devices and these were published between 1993 and 2000 [10, 13, 14, 21, 22]. These studies have significant limitations, as only patients with fractures of the ankle and the calcaneus have been included. Even if the impulse foot- or hand-pump systems can be used in fractures of the upper extremity and the tibial head, tibial shaft and tibial pilon, there are no studies available for these anatomical regions. In 2008, Khanna et al. conducted a comprehensive review of the evidence for the use of IPC devices in the healing of fractures and soft tissue injuries [23]. They concluded that the number of subjects in human studies is small and that adequately powered randomized controlled trials in humans are needed to produce stronger evidence that is clinically relevant.

Due to the methodological and clinical limitations of the available studies, a prospective, randomized controlled trial including a variety of injuries that have undergone both pre and postoperative assessment is needed to confirm the observed findings for both the lower and upper extremities. In addition, the design of the impulse foot- and hand-pump system has been renewed (VADOPlex, Vascular Impulse Technology (VIT) system, Fa. OPED, Fig. 1) and data are not yet available for the latest generation of this system.

### Objectives and hypotheses

The primary study parameter is the time to operability of the injured extremity with respect to the surrounding soft tissue. The primary hypothesis of this study is that patients using the VIT system can receive surgical treatment 2 days earlier than patients with elevation due to faster reduction of soft tissue swelling. As mentioned before, the only available data in the medical literature regarding the use of the VIT system pertain to the treatment of ankle and calcaneal fractures. Therefore, the primary study hypothesis can only be investigated in patients with fractures of the ankle, calcaneus and tibial pilon.

## Methods/design

### Design of the study and setting

A prospective, monocenter, randomized controlled trial with a parallel-group design is planned to show superiority of the VIT system compared to elevation of the injured extremity. This study will enroll participants with distinct injury patterns that are associated with severe soft tissue swelling. The study center is a level-I Trauma Center in Germany (BG Trauma Center Ludwigshafen). Trial design and management are the responsibility of the participating trauma center; biostatistical planning and analysis will be performed by the Institute of Medical Biometry and Informatics, University of Heidelberg.

### Screening

Patients with injury of the lower extremity (fractures of the tibial head, tibial shaft or tibial pilon, ankle, calcaneus) or of the upper extremity (fracture of the proximal humerus, distal humerus, distal radius or dislocation of the elbow) that cannot be treated surgically within the first day due to soft tissue swelling will be recruited for this trial. After being informed about the study and its potential risks, all individuals with an appropriate injury pattern will be consecutively screened for eligibility according to the inclusion and exclusion criteria until the recruitment period is over.

### Subject inclusion criteria

Patients older than 17 years and younger than 81 years of ageWritten informed consent provisionOne of the following nine injury types with the need for a preoperative inpatient treatment and the need for subsequent open reduction and internal fixation (fractures are classified according to the Comprehensive Classification of the OTA/AO [24]):Intra-articular calcaneal fractureAnkle fracture type 44B/CTibial pilon fracture type 43B/CDistal radius fracture type 23/CSimple/complex elbow dislocationDistal humerus fracture type 13B/CProximal humerus fractureTibial head fracture type 41B/CTibial shaft fracture

### Subject exclusion criteria

Patients younger than 18 years or older than 80 years of ageInjury of the contralateral extremityOpen fracture/dislocationInfectionLack of written informed consentSevere heart failureAcute phlebitisAcute thrombosis or pulmonary embolismLocal problems of the skin (necrosis, bladder)Drug abuseServing a gaol sentencePregnancyParticipation in another interventional trial with interference of intervention and outcome of this study

Patients will be informed about the details of the study. Informed consent comprises a description of the procedures and objectives of the study and the follow-up period. Patients will be informed that participation is completely voluntary. Participation does not confer the patient with any advantages and nonparticipation does not disadvantage the patient in any way. The use by the trial of an already-accredited and CE-certified product will be explained in detail. Potential adverse events regarding the application of the VIT system will also be explained. The participants must provide their consent for the study and for the follow-up. Participants will be instructed to report any exceptional events immediately to the study center. Screening will be performed by the principal investigator or the subinvestigator. A Case Report Form (CRF) will be prepared and will be used for the whole investigation.

### Randomization

For each of the nine injury types a separate randomization to the two intervention groups (VIT group or control group) will be performed. The randomization numbers will be allocated in balanced blocks with varying size (permuted blocks) in a 1:1 ratio using the web-based software “Randoulette” provided by the Institute of Medical Informatics, Statistics and Documentation of the Medical University of Munich (https://wwwapp.ibe.med.uni-muenchen.de/randoulette/index.jsp). This software allows different randomization methods to be chosen as well as different sets of parameters for the chosen method. To avoid any potential of predicting the group allocation of future patients, the block length is recorded in a separate document that is withheld from the study site.

In addition, persons with the right to randomize with the software described above do not have the right to read or edit the randomization design chosen within the software. The software stores the result of randomization and the patient’s characteristics as well as the name of the person who randomized and the randomization date in a separate file, and only authorized persons can download this file. Patients are randomized on the day of inclusion in the study. Blinding of the patients and the assessors is unfeasible. The investigators will perform the assessment according to trial criteria.

### Interventions

The patients included will be randomized in a 1:1 ratio either into the VIT group or into the control group in each of the nine injuries separately. Patients of the VIT group will receive a short instruction regarding the use of the already-accredited and CE-certified VIT system. Afterwards, the VIT system will be applied to the foot in the case of a lower extremity fracture or to the hand in the case of an upper extremity injury. The therapy interval of pneumatic compression will be chosen as recommended by the company: 24 h a day in the preoperative period and 6 to 8 h in the postoperative period. In the control group the injured extremity will be splinted and elevated for 24 h a day in the preoperative period. In the postoperative period the time of elevation is recommended according to the soft tissue swelling. In both groups the duration of the therapy (pneumatic compression or elevation) will be documented during the daily study visits. In all patients, no further antiswelling interventions, such as lymphatic drainage, will be applied. The primary investigator will perform an interim analysis regarding the presence of adverse events and dropouts after the inclusion of the first 30 patients. In case of the occurrence of any adverse event related to the study, the responsible local Ethics Committee will be informed to decide whether the study can by continued or not. No forms of nonignorable clustering regarding the primary outcome parameter have been detected during planning of the study.

### Evaluation

The primary outcome parameter (time to operability) will be assessed day-to-day by one of two independent experienced orthopedic senior consultants, who will define whether the soft tissue permits definite surgical treatment of the fracture, irrespective of other reasons that do not allow surgical treatment. These independent examiners are not involved with the design of the study. The definition of operability is decided by these blinded examiners based on two basic rules: (1) that there is crumpling of the skin at the surgical side and (2) that suturing of the skin without tension will be possible after definitive operative treatment. For the assessment of the primary outcome parameter, the time from injury to the first day of operability will be documented regardless of the time of definitive surgical treatment.

The time schedule of the study and the primary and secondary outcome parameters and respective measurements are shown in Table 1 and Fig. 2. The final follow-up will be obtained 14 (±4) days after the patients have been formally discharged.

**Table 1 Tab1:** Please check if we have captured the tables correctly.Study outcome measures of the Vascular Impulse Technology (VIT) study

Item	Outcome measurement	Measurement point	Primary/secondary outcome parameter
Operability	Time from injury to operability (days)	Daily visit preoperatively	Primary
Soft tissue swelling	Girth measurements of the injured and the uninjured contralateral extremity (cm)	Daily visit pre and postoperatively and 14 days after submission	Secondary
Pain level	Visual Analog Scale (VAS)	Daily visit pre and postoperatively and 14 days after submission	Secondary
Pain medication	Substance and dosage of painkillers	Daily visit pre and postoperatively and 14 days after submission	Secondary
Complications	Detailed description of complications	Daily visit pre and postoperatively and 14 days after submission	Secondary
Revision surgeries	Detailed description of revision surgeries	Daily visit postoperatively and 14 days after submission	Secondary
Duration of total hospital stay	Days	At the day of submission	Secondary

**Fig. 2 Fig2:**
[figure not shown]
Content for the schedule of enrollment, intervention and assessments for each of the nine injury types (SPIRIT figure)

### Sample size

The prior assumptions for sample size calculation are based on the results of Caschman et al. and Keehan et al. and assume a decrease of the mean time from injury to operability of 2 days in the VIT group compared to the control group [10, 20]. Allowing for an assumed standard deviation of 2 days and that 15% of the patients in each group will be lost to follow-up then a total of 20 patients (17 patients + 3 patients assumed to dropout) is required in each group to ensure an 80% chance of significant detection (at the 5% level based on a two-sided *t* test). The sample size calculation based on the results of Caschman et al. and Keehan et al. can be used for three of the nine injury types: the calcaneal fracture, the ankle fracture and the tibial pilon fracture. In these three injury types 40 patients will be included, respectively. For the other six injury types a sample size calculation is not possible due to a lack of data in the medical literature. Therefore, in the other anatomical regions a sample size calculation was obtained from the institutional data from the year 2014 (Table 2). It is estimated that 30% of the patients can be recruited after checking the inclusion and exclusion criteria. Taking the institutional data from the year 2014 into account, 30 patients with distal radius fracture, 16 patients with elbow dislocation, 14 patients distal humerus fracture, 30 patients with proximal humerus fracture, 40 patients with tibial head fracture and 30 patients with tibia shaft fracture will be included in the study. The number of patients who will be randomized in each of the nine injury types is shown in Table 2. In total, 280 patients will be included in nine separate studies according to the nine different injury types. The study length for recruitment is expected to be 2 years. The follow-up period is 14 days after discharge from hospital treatment.

**Table 2 Tab2:** Sample size calculation

Injury	Number of patients in 2014 at the study center	Number of patients included in the planned study
Calcaneal fracture (intra-articular)	119	40^a^
Ankle fractures: type 44B/C	106	40^a^
Tibial pilon fracture: type 43B/C	64	40^a^
Distal radius fracture: type 23C	102	30^b^
Tibial shaft fractures	100	30^b^
Elbow dislocations (simple and complex)	55	16^b^
Distal humeral fractures: type 13B/C	46	14^b^
Proximal humeral fractures	99	30^b^
Tibial head fractures: type 41B/C	138	40^b^
Total		280

^a^sample size calculation are based on the results of Caschman et al. [20]; ^b^sample size calculation based on the treated patients in 2014 in the study center

### Statistical methods

Descriptive statistics (mean, standard deviation, median, interquartile range, absolute and relative frequencies) will be calculated to characterize the study population. A separate analysis for each of the nine injury types will be performed. The primary outcome parameter, the time from injury to operability (in days) will be assessed using a *t* test. In addition, a sensitivity analysis with the nonparametric Mann-Whitney *U* test will be performed. In addition, Kaplan-Meier survival curves for descriptive analysis of the primary outcome parameter will be visualized. For continuous secondary variables a *t* test will be applied, possible differences of categorical endpoints will be analyzed using chi-square tests. A *p* value < 0.05 is considered as statistically significant. Univariate and multivariate regression analyses will be performed to investigate the influence of parameters, such as age, gender and affected side, on the outcome. The primary outcome parameter will be assessed day-to-day by one of two independent experienced orthopedic senior consultants. To validate the agreement of the assessment of the two examiners, the exact agreement regarding the binary variable (operability: yes or not) on 10 consecutive patients will be assessed each day from randomization to definitive surgical treatment. The exact agreement of both examiners regarding the primary outcome parameter should be at least 90%.

The intention-to-treat principle will be adopted: patients will be analyzed according to their initial treatment group in case of crossover to the other group. A sensitivity analysis with a per-protocol analysis will be performed to assess the robustness of the results.

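### The primary t test ignores the pre-randomisation delay and initial swelling; adjusting for them should gain precision in the seven strata of 30 to 40 patients

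*Protocol article*

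**What the plan says.** **Analysis.** Under Statistical methods: "The primary outcome parameter, the time from injury to operability (in days) will be assessed using a" t test. The back-up is also unadjusted: "In addition, a sensitivity analysis with the nonparametric Mann-Whitney" U test. Both are run stratum by stratum: "A separate analysis for each of the nine injury types will be performed". Regression models are planned "to investigate the influence of parameters, such as age, gender and affected side, on the outcome", but they are not tied to the primary comparison, and neither swelling nor delay is among the examples. Continuous secondary outcomes get a plain t test.

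**Outcome clock.** Evaluation counts days from injury to the first day of operability. Randomization says: "Patients are randomized on the day of inclusion in the study". The software stores that date.

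**Swelling.** Table 1 lists "Girth measurements of the injured and the uninjured contralateral extremity (cm") at daily visits before and after surgery. No visit is marked as preceding the start of treatment. The Discussion justifies the primary outcome on the ground that swelling before surgery is its main determinant.

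**Sample size.** The calculations "assume a decrease of the mean time from injury to operability of 2 days in the VIT group compared to the control group", with SD 2 days, a two-sided 5% t test and 80% power. This gives 17 evaluable and 20 enrolled per group in three injury types. The other strata range from 14 to 40 patients.

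**The concern.** Time from injury to operability is the sum of two parts: injury to randomisation, and randomisation to operability. The first part is fixed before allocation and can only add noise to the comparison. The second should depend on how swollen the limb was at the start, because operability is judged by skin crumpling and by whether the wound can be closed without tension. The planned test leaves both sources of variation in the residual.

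What is at stake is the width of the confidence interval in nine small, separate analyses. The same applies to girth and pain VAS, which are compared without their starting values.

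**Working it through.** **Inputs.** From Sample size: difference 2 days, SD 2 days, two-sided 5%, 17 evaluable per arm. From Table 2: four strata of 40, three of 30, one of 16 and one of 14. The multiple correlation r of the covariates with the outcome is not in the protocol; 0.3, 0.5 and 0.6 are assumed, so R² = r² = 0.09, 0.25 and 0.36.

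**Step 1: the plan's own figure.** SE = 2·√(2/17) = 0.686; noncentrality 2/0.686 = 2.92; df = 32. The noncentral t gives power 0.807 at 17 per arm and 0.781 at 16. So 17 is right, and 17/0.85 = 20 enrolled. The stated figure reproduces.

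**Step 2: adjusted model with k covariates.** Residual SD = 2·√(1−R²); df = 2n−2−k; the variance is multiplied by 1 + k/(2n−3−k) for expected chance imbalance in the covariates. For n = 17, k = 2, r = 0.5: SE = 2·√0.75·√(2/17)·√(1+2/29) = 0.614; noncentrality 3.26; df 30; power 0.883.

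| n per arm | Unadjusted | r = 0.3 | r = 0.5 | r = 0.6 |
|---|---|---|---|---|
| 17 (stratum of 40 after dropout) | 0.807 | 0.816 | 0.883 | 0.926 |
| 15 (stratum of 30) | 0.753 | 0.758 | 0.834 | 0.887 |
| 8 (stratum of 16) | 0.461 | 0.426 | 0.497 | 0.561 |
| 7 (stratum of 14) | 0.406 | 0.361 | 0.423 | 0.481 |

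The protocol's difference and SD are carried into the other strata for illustration only. A simulation of 10,000 trials at R² = 0.3 agrees with the formula: 0.81 unadjusted against 0.90 adjusted at 17 per arm, and 0.40 against 0.46 at 7 per arm.

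**Step 3: break-even.** Two covariates pay once R² exceeds about 0.06 at 20 per arm, 0.07 at 17 and 0.08 at 15. After 15% dropout a stratum of 30 has 0.85 × 15 = 12.75 per arm; at 12 the threshold is 0.10. At 8 and 7 per arm it is 0.17 and 0.21. With one covariate (k = 1 in the same formula) the thresholds at 8 and 7 per arm are about 0.09 and 0.11.

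**Step 4: the cost if the covariates are useless.** At R² = 0 and 17 per arm, power falls from 0.807 to 0.779.

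**Step 5: chance imbalance.** The typical shift in the estimate due to the covariates is about r times its SE: 0.3 × 0.686 = 0.21 days to 0.6 × 0.686 = 0.41 days. The unadjusted SE already contains this.

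**Reach.** The strata of 30 to 40 hold 4 × 40 + 3 × 30 = 250 of 280 patients, including the three (ankle, calcaneus, pilon) that carry the primary hypothesis.

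**The case against.** The strongest reply is that nothing here is broken. Allocation is 1:1 within each injury type, so the t test is valid; the days before randomisation add noise, not bias; and the sample size was computed for the same test. All of that stands. A reader might infer that the unadjusted comparison is biased or the trial underpowered because of it. The protocol supports neither reading.

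A reader might also take both covariates as already recorded before treatment. The protocol does not say so. Girth is a daily preoperative measurement with no stated value before treatment, and the delay has to be derived from two dates. Adjusting for a girth taken after the device was started could remove part of the treatment effect.

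Nor is precision given away in every stratum. With 7 or 8 per arm, two covariates lose power at r = 0.3 and r = 0.4 (7 per arm: 0.406 falls to 0.36–0.39; 8 per arm: 0.461 falls to 0.43–0.455).

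Finally, the correlation is unknown. The Discussion's remark concerns swelling over the preoperative period, not one first-visit girth, and the spread of the delay is not given. This limits how large a gain can be promised.

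One argument carries less weight: that covariates may be left to an analysis plan. The protocol positively fixes the primary test as a t test, so this is a stated choice that can be improved.

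**Conclusion.** The point holds as a recommendation about efficiency. The outcome contains a component that treatment cannot alter, and the protocol itself names swelling as its main driver, yet the primary comparison uses neither.

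The gain at 17 per arm runs from about one percentage point of power (r = 0.3) to about 12 (r = 0.6). At 15 per arm it runs from under one point to about 13. These sizes rest on the protocol's difference and SD, on assumed correlations, and on a girth value that truly precedes treatment. If the covariates explain less than about 6–8% of the variance (about 10% in strata of 30 after dropout), there is a small loss instead. For the strata of 14 and 16 the two-covariate model is not recommended.

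**What to change.** - **Strata of 30 to 40:** make the primary test the treatment coefficient in a linear model of time to operability on treatment, days from injury to randomisation, and injured-minus-contralateral girth at the first visit. Specify that this girth is taken before the device or elevation starts under the allocated treatment. If no such value exists, adjust for the delay only.
- **Strata of 14 and 16:** use at most one covariate, the delay, or keep the t test. Decide which in advance.
- **Sensitivity analyses:** keep the unadjusted t test and the Mann-Whitney U test.
- **Secondary outcomes:** adjust the girth and pain VAS comparisons for their values before treatment.

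The planned sample size need not change. The statistical cost is two degrees of freedom per model, and the small power loss shown above if the covariates prove weak. The delay follows from the injury date, which the outcome already requires, and the stored randomisation date. The girth covariate may need more than analysis wording, because a measurement before treatment has to be defined in the visit schedule and CRF. The article says enrolment is about to start, so this is best settled before the first patient.

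### One unadjusted p < 0.05 significance rule covers six secondary outcomes in nine separate injury-type analyses, with no order, gating or exploratory label

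*Protocol article*

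**What the plan says.** Table 1 (Protocol article, Evaluation) marks one outcome as primary and six as secondary: girth, pain on a visual analog scale, pain medication, complications, revision surgery and total hospital stay. Girth, pain, pain medication and complications share the same measurement schedule, "Daily visit pre and postoperatively and 14 days after submission".

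The Statistical methods section fixes three things that act together:

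- On the unit of analysis: "A separate analysis for each of the nine injury types will be performed".
- On the secondary tests: "For continuous secondary variables a *t* test will be applied, possible differences of categorical endpoints will be analyzed using chi-square tests".
- In the next sentence, a p "value < 0.05 is considered as statistically significant". This threshold is not tied to any particular outcome.

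The same section does restrict some other analyses by name. The Kaplan-Meier curves are descriptive, and the Mann-Whitney and per-protocol analyses are sensitivity analyses. The secondary tests and the regression analyses carry no such restriction.

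**The concern.** As written, every secondary p value below 0.05, in any of the nine injury types, qualifies as a statistically significant finding. The article gives no order among the secondary outcomes, no adjusted threshold and no requirement that the primary test in that type succeed first.

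The secondary outcomes are not incidental to the trial's case. The Background says of earlier work on the foot pump that "complications such as postoperative skin necrosis and compartment syndrome, and the amount of pain medication required have not been determined". A significant difference in complications or analgesic use would therefore be read as an answer to a stated evidence gap.

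At stake is a report that claims, say, less pain or a shorter stay in one fracture type where the primary outcome shows nothing, on evidence that chance alone would often produce. The point concerns the secondary outcomes only, not the nine tests of the primary outcome.

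**Working it through.** **The plan's own figures.** The article gives no error rate for the secondary outcomes. Its only related calculation is the primary sample size, and that reproduces. With a difference of 2 days, SD 2 days and a two-sided 5% t test, 17 per group gives 80.7% power, and 17 / 0.85 = 20 per group after 15% dropout. This calculation covers the primary outcome only.

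**Inputs**

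- Secondary outcomes: 6 (Table 1).
- Separate analyses: 9 (Statistical methods).
- Threshold: 0.05 (Statistical methods). The article states sidedness only in Sample size, "at the 5% level based on a two-sided" test. I assume the secondary tests are two-sided as well.
- Tests: 6 × 9 = 54, taking one test per outcome per type.
- Null case: no true difference on any secondary outcome.
- The nine types contain different patients, so they are treated as independent.
- Correlation between the six test statistics within a type is not given. I assume 0, 0.5 and 0.8.

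**Independent tests**

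- Any false significant result: 1 − 0.95^54 = 0.937. Expected number: 54 × 0.05 = 2.7.
- Any false benefit for VIT (half of each two-sided level): 1 − 0.975^54 = 0.745. Expected number: 54 × 0.025 = 1.35.
- One injury type: 1 − 0.95^6 = 0.265 in either direction and 1 − 0.975^6 = 0.141 for a false benefit.
- The three types to which the primary hypothesis is limited (18 tests): 1 − 0.95^18 = 0.603 and 1 − 0.975^18 = 0.366.

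**Correlated tests.** The six statistics within a type are taken as equicorrelated normals. If q is the chance of at least one false result within a type, the chance over nine types is 1 − (1 − q)^9.

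| Assumed correlation | One type, either direction | One type, false benefit | Nine types, either direction | Nine types, false benefit |
|---|---|---|---|---|
| 0 | 26.5% | 14.1% | 93.7% | 74.5% |
| 0.5 | 20.7% | 10.4% | 87.6% | 62.7% |
| 0.8 | 13.9% | 6.9% | 73.9% | 47.6% |

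**Small strata.** A chi-square test on an uncommon event with 7 to 20 patients per group does not reject at exactly 5%. I treated complications and revisions as yes/no outcomes, with assumed null rates of 10% to 44% and 5% to 10%, and left the other four outcomes at 5%. All tests were taken as independent. The nine-type figures become:

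- Without continuity correction: 88% to 92% in either direction, 65% to 72% for a false benefit.
- With continuity correction: 85% to 87% and 60% to 63%.

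**The case against.** **The family of 54 is a choice.** The Sample size section describes nine separate studies, each type is randomized separately, and no claim across types is planned. On that view the relevant family is six tests, and the error is 14% to 26.5% in either direction, or 7% to 14% for a false benefit. This stands as a reason to report the per-type figures. Even so, the either-direction figures are about three to five times the nominal 5%, and the false-benefit figures about three to six times the nominal 2.5%.

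**Not every outcome has a defined test variable.** Complications, revisions and painkillers are recorded as descriptions or as substance and dosage. Counting only girth, pain and hospital stay gives 27 tests. If these are independent, the chances are 1 − 0.95^27 = 75.0% in either direction and 1 − 0.975^27 = 49.5% for a false benefit. The size falls, but the point remains.

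**The outcomes are already called secondary, and an analysis plan may add detail.** Both are fair, and both lower the severity. However, the article does more than stay silent: it states a significance rule and places it directly after the secondary tests. An analysis plan that restricted the rule would have to depart from the published text.

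**Two stronger readings are not supported.** A reader might infer that a false secondary benefit is almost certain. The 94% counts false results in both directions, including those favouring elevation, and assumes independence. A false benefit has at most about a 75% chance with 54 tests. A reader might also multiply the count by the pre-operative, post-operative and follow-up visits. Table 1 lists when data are recorded, but nothing says that each phase is tested, so I do not use a larger count.

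**Conclusion.** The point holds as a fault in the stated significance rule. If all secondary nulls are true and there is one test per outcome and type, a false significant result somewhere is likely: about 94%, falling to 74% at a correlation of 0.8. A false benefit for VIT has a chance of roughly 75% to 48%.

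These sizes rest on the assumed correlations and two-sided tests. They would be somewhat lower with discrete chi-square tests, and lower again if the device truly affects some outcomes, because fewer nulls would then be true.

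The primary analysis and its sample size are not called into question. What is limited is how far the trial may go in interpreting secondary results.

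**What to change.** In Statistical methods, restrict the 0.05 significance rule to the primary-outcome analysis. Add a sentence such as: 'Analyses of secondary outcomes and the regression analyses are exploratory; they will be reported as estimates with 95% confidence intervals and descriptive p values, without claims of statistical significance.'

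A fixed testing sequence for one or two named secondary outcomes is possible if the investigators want a confirmatory secondary claim, but it is a trade-off and is not needed to resolve this point.

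The cost is one or two sentences, with no added patients or data. According to Trial status, enrolment is only about to start, so the change can be made before any results exist. The downside is small: isolated secondary p values below 0.05 could no longer be reported as significant effects.
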